### Sample size

2.4

The initial assessment of sample size is based on taking peri-hematoma rCBF as the ischemic reign of brain tissue.^[14]^ For no study now available referring to the field, the pilot trial was conducted to assess the sample size.

The pilot data includes 12 patients (6/each group) and shows the rate of reduction of peri-hematoma rCBF are (0.4282 ± 0.14705) and (0.3555 ± 0.12592) in intensive/conservative BP-lowering group, compared with that of contralateral homologous reign. For the reduction of relative rCBF, ≥44%^[28]^ is regarded as a threshold of infarction, if the difference of 2 groups is more than 9% (9%+35.5%>44%); acute SBP lowering is considered to significantly increase the risk of infarction in these patients. So, each sample size of 36 in a group will be required to detect a significant difference of 5% (2-tailed) and a power of 90% (PASS software Version 11.0.4; NCSS). In view of 10% patients lost to follow-up, a total of 80 patients (40 in each group) will be included in this trial.

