Theoretically, the conservative antihypertensive treatment (<180 mm Hg) is safe and may be beneficial to the sICH patients with cerebrovascular stenosis. The patients undergoing conservative antihypertensive treatment may have higher peri-hematoma rCBF and lower incidence of brain ischemia or infarction, which are associated with neurological deterioration or mortality. Moreover, long-term outcome may be better for the neuroprotection after the conservative antihypertensive treatment. Thus, a well-designed clinical trial is need to assess the safety and efficacy of intensive SBP lowering for sICH with cerebrovascular stenosis, and provides powerful evidence to clinical practice. Here, we described a parallel, superiority, randomized, assessor-blinded trial termed antihypertensive treatment in patients of sICH with cerebrovascular stenosis trial (ATICHST).

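### The stated 90% power does not follow from the protocol's own inputs: 36 per group gives about 79% for a 9-point difference

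*Protocol article*

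**What the plan says.** All the sample-size inputs are in section 2.4 of the protocol article.

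- **Pilot:** "The pilot data includes 12 patients (6/each group"), with results given as "0.4282 ± 0.14705) and (0.3555 ± 0.12592) in intensive/conservative BP-lowering group". The outcome is the relative reduction of peri-hematoma rCBF against the mirror region.
- **Difference of interest:** derived from a 44% infarction threshold, as "if the difference of 2 groups is more than 9% (9%+35.5%>44"%).
- **Error rates and size:** "each sample size of 36 in a group will be required to detect a significant difference of 5% (2-tailed) and a power of 90" per cent, attributed to PASS 11.0.4. This is raised to 40 per group, 80 in total, for 10% loss to follow-up.

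Section 2.9 (Statistical analysis) names the t test for continuous outcomes. Section 2.7.4 makes this outcome the key primary one. The Background calls the study "a parallel, superiority, randomized, assessor-blinded trial", while the Aim and both conclusion statements speak of the safety and effectiveness of intensive lowering.

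**The concern.** The protocol prints a difference, two SDs, a significance level, a power and a sample size. These five must agree, and they do not: the sample size is too small for the stated power. This is a conflict between stated figures, not a detail left to a fuller document.

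It is the only justification of the trial's size, and it concerns the key primary outcome. The direction of the error also matters. The outcome measures possible harm from intensive lowering, so low power favours a finding of no difference. In a trial that says it will determine safety, readers who trust a 90% power statement could take a non-significant result as reassurance the data do not give.

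**Working it through.** **Inputs (section 2.4):** difference d = 0.09; SDs 0.14705 and 0.12592; two-sided 5%; stated power 90%; n = 36 per group; 10% loss. The 5% is read as the significance level. Test: two-sample t (section 2.9).

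**Step 1. Variance.**
0.14705² + 0.12592² = 0.021624 + 0.015856 = 0.037480.
Pooled SD = √(0.037480 / 2) = 0.1369.

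**Step 2. Try to reproduce the plan's 36.** Normal formula: n = (1.96 + z)² × 0.037480 / 0.09², where 0.037480 / 0.0081 = 4.627.

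- 90% power: (1.96 + 1.2816)² × 4.627 = 10.51 × 4.627 = 48.6, so 49 per group. The noncentral t gives 50.
- 80% power: (1.96 + 0.8416)² × 4.627 = 7.849 × 4.627 = 36.3, so 37 per group. The noncentral t gives 38.

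The stated 36 is not reproduced at 90%. It lies within 2 patients of the 80% answer.

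**Step 3. Power at 36 per group.** SE = √(0.037480 / 36) = 0.03227, and 0.09 / 0.03227 = 2.789.

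- Normal: Φ(2.789 − 1.960) = Φ(0.829) = 79.7%.
- Noncentral t with equal variances: 78.5%. Welch: 78.5%.
- All 40 per group evaluable (t test): 82.7%.

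**Step 4. Can another reading give 36 at 90%?** Figures are for the t test unless marked.

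| Reading | n per group for 90% | Power at 36 |
|---|---|---|
| 9 points, pooled SD, two-sided | 50 | 78.5% |
| 9 points, smaller SD for both groups | 43 | 84.9% |
| 9 points, larger SD for both groups | 58 | 72.6% |
| 9 points, pooled SD, one-sided 5% | 41 | 86.8% |
| 8.45 points (44% − 35.55%), pooled SD | 57 | 73.3% |
| 7.27 points (pilot difference, 42.82% − 35.55%), pooled SD | 76 | 60.3% |
| 5% read as the difference, pooled SD (normal) | 158 | not computed |
| 9 points, smaller SD and one-sided 5% | 35 | 91.3% |

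Only the last row reaches 90% with 36. It contradicts the stated two-tailed test and ignores the SD of the intensive group.

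**Step 5. What 36 per group would need for 90% (t test).** Either an SD of 0.116, below both pilot SDs, or a difference of 10.6 points.

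**Step 6. Loss to follow-up.** 36 / 0.9 = 40 per group, 80 in total. This step is correct. From the right starting point, 50 / 0.9 = 55.6, so 56 per group and 112 in total.

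**Step 7. What a null result would show.** With SD 0.1369 and 36 per group, the 95% CI half-width is 1.994 × 0.03227 = 0.064, or 6.4 points. The upper limit falls below 9 points only if the observed difference is below about 9 − 6.4 = 2.6 points. An observed difference between 2.6 and 6.4 points would be non-significant and still compatible with a 9-point harm.

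**Step 8. Uncertainty of the SD.** With 10 degrees of freedom, the 95% CI for the SD runs from 0.1369 × √(10 / 20.48) = 0.096 to 0.1369 × √(10 / 3.247) = 0.240. Power at 36 per group then ranges from 98% to 35%.

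**The case against.** The arithmetic is not in dispute. The other side's case concerns what is built on it.

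- **Cause of the error.** The normal formula rounds up to 37 and the t test needs 38, so 36 does not quite reach 80% either. The software inputs are not printed, and another SD may have been used. This stands: the mismatch is certain, while a mislabelled 80% calculation is only a plausible explanation.
- **The 9-point target.** It comes from the infarction threshold, not from the pilot difference, and 35.5 + 9 = 44.5 does exceed 44. This also stands. The target is a legitimate choice and not a second defect. The figures at 8.45 and 7.27 points show sensitivity only.
- **SD uncertainty.** The 98% to 35% range contains 90%, so it does not prove the error. That is correct, but it does not rescue the claim: 90% still does not follow from the values the protocol chose.
- **Practical size.** The perfusion scan takes place about 24 hours after randomization, so losses may be below 10%. Power would then lie between 79% and 83%, near a common design level. This tempers the consequence: the design is not unfit, but the stated figure is still wrong.
- **Reading of a null result.** No passage says a non-significant result will be called safe, and a confidence-limit rule goes beyond an arithmetic correction. That is fair as far as it goes. The rule does, however, use the protocol's own 9 points and serve its stated safety aim, and the correction of the power stands without it.

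**Conclusion.** The stated power is wrong as written. Taking the protocol's 9-point difference and pilot SDs at face value, with a two-sided 5% t test, 36 evaluable per group give about 79% power. That is more than 10 percentage points below the claim, and the type II error is about twice the implied 10%. Even with no losses, power is 83%. The requirement for 90% is 49 to 50 evaluable per group.

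The result assumes that the printed inputs are the ones intended. If the calculation used others, the protocol does not give them and section 2.4 still fails to support its own figure. The correction is needed because this is the sole basis for the trial's size on its key primary outcome.

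**What to change.** 1. **Restate section 2.4.** With 80 randomized and 36 evaluable per group, the trial has about 79% power for a 9-point difference at two-sided 5%, or 90% power for 10.6 points. Give the power at the pilot difference as well (60% at 7.3 points), and report the exact software inputs.
2. **Add one sentence on interpretation.** No important reduction is claimed only if the upper 95% confidence limit for the difference (intensive minus conservative) is below 9 points. Any other non-significant result is inconclusive.

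The cost is wording in the protocol and in any analysis plan, plus a less favourable power figure. No more patients are needed. If the sponsor prefers to keep 90% power for 9 points, the alternative is about 50 evaluable per group, or 112 randomized: 32 more than planned.

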### Randomization

2.5

Patients are assigned to intensive BP-lowering group and conservative BP-lowering group by a minimization random allocation system (minimpy 0.3). They are stratified by level of stenosis and location of stenosis. All information of patients is collected and randomization is stratified by a special researcher within 1 hour after admission in department of emergency. Once the group is determined, the allocation is not allowed to change unless quit from the trial.

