#### Inclusion criteria

2.3.1

(1)Age ≥18 years;(2)Randomized to groups within 6 hours from onset;(3)Acute spontaneous ICH, verified by noncontrast CT (NCCT) or magnetic resonance imaging;(4)Cerebrovascular luminal narrowing (30–70%) demonstrated with CT angiography (CTA) upon admission;(5)SBP is from 150 to 220 mm Hg (twice repeat measurements, record ≥2 minutes apart)

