#### Intensive group

2.7.1

All patients receive a standardized, stepped, continuous intravenous infusion of antihypertensive agents and frequent BP monitoring. On the basis of the 2015 guidelines of American Heart Association (AHA),^[29]^ the SBP intensive group is to maintain below 140 mm Hg within 1 hour from randomization. The intravenous antihypertensive agents included nitroglycerin, nicardipine, and urapidil hydrochloride. With the use of oral antihypertensive agents after the safety evaluation by doctor group, the doses of intravenous antihypertensive agents are reduced gradually. SBP is maintained from 120 to 140 mm Hg for following 7 days or until hospital discharge if this occurred in advance. About 120 mm Hg is considered as the safe threshold value, lower than which patients may have a risk of low BP. When SBP is lower than 120 mm Hg, we will reduce the velocity of infusion and adjust it according to repeated measurements of BP until SBP maintaining 120 to 140 mm Hg. All of antihypertensive agents are stopped when SBP is lower than 90 mm Hg, and antihypotensive treatments will initiate if necessary. The oral antihypertensive agents are suggested to use to maintain the BP <140 mm Hg upon discharge.

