#### Conservative group

2.7.2

The goal of conservative group is to maintain SBP from 140 to 180 mm Hg within 1 hour after randomization. The intermittent or continuous intravenous antihypertensive agents are used to maintain the SBP from 140 to 180 mm Hg and be examined again every 15 minutes. When SBP is more than 180 mm Hg, we will increase the dose of antihypertensive agents or combine different antihypertensive agents.

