#### Primary outcomes

2.7.4

The relative reduction of the perihematoma rCBF is considered as the key primary outcome. Relative reduction of rCBF = 1-(rCBF / contralateral homologous regions rCBF).^[14]^ The other primary outcomes include absolute CBF, Tmax, mean transit time (MTT), and rCBV of perihematoma region, those indexes of global and hemisphere, the rate of ischemic stroke within 7 days, volumes of parenchymal hematoma, IVH, and ischemic region.

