### Statistical analysis

2.9

The analysis of this study is based on the intention-to-treat principle. The continuous variable of primary outcome and second outcomes will be assessed by *t* test. The Chi-square test will be used to assess the categorical data of second outcomes. Log-rank test will be used to analyze the time-to-event type of outcomes. Subgroup analysis will be conducted by level of cerebrovascular stenosis and location of the cerebrovascular stenosis.

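### The key primary outcome is compared by an unadjusted t test, although entry SBP, measured before allocation and deciding how far each absolute target must lower pressure, could be used as a covariate at no cost

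*Protocol article*

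**What the plan says.** - **Eligibility (2.3.1):** "SBP is from 150 to 220 mm Hg", from two readings at least 2 minutes apart.
- **Targets (2.7.1, 2.7.2):** "the SBP intensive group is to maintain below 140 mm Hg within 1 hour from randomization", followed by 120 to 140 mm Hg. For the other arm, "The goal of conservative group is to maintain SBP from 140 to 180 mm Hg within 1 hour after randomization".
- **Allocation (2.5):** minimisation, of which the protocol says: "They are stratified by level of stenosis and location of stenosis". No other factor is named.
- **Outcome (2.7.3, 2.7.4):** "The relative reduction of the perihematoma rCBF is considered as the key primary outcome". It is one minus the ratio of perihematoma to contralateral rCBF, read from one CT perfusion scan 24 ± 3 hours after randomisation. Admission imaging is described as NCCT and CTA; no perfusion scan before treatment is mentioned.
- **Analysis (2.9):** "The continuous variable of primary outcome and second outcomes will be assessed by" a t test. No covariate is named. "Subgroup analysis will be conducted by level of cerebrovascular stenosis and location of the cerebrovascular stenosis".

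Entry SBP therefore appears in eligibility but not in the allocation, the primary analysis or the subgroups.

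**The concern.** The Background and the Sample size section (2.4) argue that acute SBP lowering may reduce flow around the hematoma and raise the risk of infarction. With absolute targets, the least lowering a patient needs depends on the pressure at entry. Entry SBP is thus a baseline value with a stated reason to be related to the outcome in both arms. It is known before allocation, so adjusting for it cannot be affected by treatment. A pre-treatment value of the outcome itself would usually be the first choice of covariate, but none is described.

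An unadjusted comparison leaves any outcome variation due to entry SBP in the error term. What is at stake is the width of the interval for the key primary result, in a trial of 80 patients where a few points of power are worth having.

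**Working it through.** **1. Minimum fall to the upper limit of each target** (2.3.1, 2.7.1, 2.7.2)

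Intensive: entry − 140. Conservative: max(0, entry − 180).

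| Entry SBP (mm Hg) | Intensive | Conservative | Difference |
|---|---|---|---|
| 150 | 10 | 0 | 10 |
| 160 | 20 | 0 | 20 |
| 180 | 40 | 0 | 40 |
| 200 | 60 | 20 | 40 |
| 220 | 80 | 40 | 40 |

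These are minimum falls from the entry reading, not the pressures at the time of the scan.

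**2. The plan's own sample size** (2.4)

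Inputs: pilot SDs 0.14705 and 0.12592, difference 0.09, two-sided 5%, 90% power.

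- Pooled SD = √[(0.14705² + 0.12592²)/2] = 0.1369.
- For 90% power the t test needs 50 per arm (49 by the normal approximation). The stated 36 does not reproduce.
- At 36 per arm, SE = 0.1369 × √(2/36) = 0.0323, noncentrality = 0.09/0.0323 = 2.79, and power is 78.5%.
- The dropout step is right: 36/0.9 = 40.

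The gap between 78.5% and 90% is a separate matter. Here 78.5% is only the starting point.

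**3. Effect of the covariate**

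If entry SBP explains a share R² of the outcome variance, the residual SD is 0.1369 × √(1 − R²), with one degree of freedom lost. The protocol gives no value for R², so a range is shown.

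| Assumed R² | SE of difference | Power, 36 per arm | n per arm for 90% |
|---|---|---|---|
| 0 | 0.0323 | 78.5% | 50 |
| 0.05 | 0.0314 | 80.6% | 48 |
| 0.10 | 0.0306 | 82.6% | 45 |

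The interval narrows by 1 − √0.95 = 2.5% or 1 − √0.90 = 5.1%. Losing four degrees of freedom rather than one changes power by less than 0.1 percentage point in each row.

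**4. Is an R² of 0.05 to 0.10 reasonable?**

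Suppose, purely for illustration, that entry SBP is uniform over 150 to 220 (SD 70/√12 = 20.2) and that the whole 0.09 effect is proportional to the minimum fall.

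- Mean difference in fall = (30/70) × 25 + (40/70) × 40 = 33.6 mm Hg, so the slope is 0.09/33.6 = 0.00268 per mm Hg.
- Intensive arm: (0.00268 × 20.2)²/0.1369² = about 16% of the variance.
- Conservative arm: the SD of max(0, entry − 180) is 13.2 mm Hg, so (0.00268 × 13.2)²/0.1369² = about 7%.

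The average is about 11%. That takes the trial's hypothesis at full strength, so 5% to 10% is a fair range and 0 remains possible.

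**5. Chance imbalance**

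For an assumed entry SD of 15 to 20.2 mm Hg and 36 per arm, the SE of the difference in mean entry SBP is SD × √(2/36) = 3.5 to 4.8 mm Hg, a 95% range of about ±7 to ±9. The resulting shift in the rCBF difference has a 95% range of 1.96 × √R² × 0.0323, that is ±0.014 at R² = 0.05 and ±0.020 at R² = 0.10, against a target of 0.09. The t test's standard error already allows for this; adjustment removes it.

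**The case against.** The strongest reply is that nothing here is wrong. After random allocation a t test is unbiased whatever prognostic factors it omits, and chance imbalance is already counted in its standard error and error rate. This stands. A reader might infer that the planned result would be biased or its type I error inflated; the documents do not support that. Nor does the omission by itself make the sample size wrong: if the pilot used the same entry range, its SDs already contain the spread due to entry SBP.

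The link to the outcome is also unproven. The outcome is a within-patient ratio to the opposite side, so an effect of pressure common to both sides partly cancels. The Background reports that ADAPT found no fall in perihematoma rCBF after intensive lowering. The trial's premise puts the risk in the stenosis, which makes the two chosen minimisation factors coherent. So entry SBP cannot be called the baseline value most closely tied to the outcome, and an R² of zero stays in the range.

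It is also tempting to say that patients entering at or below 180 mm Hg are compared on lowering versus no lowering. That goes too far. The Background states that the highest SBP appears at 24 hours after onset, and patients are randomised within 6 hours, so a conservative-arm patient may rise and need treatment later.

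Finally, covariate lists are often left to the SAP. But section 2.9 does name the primary test, so the point is a specific improvement to a stated choice and not a complaint about missing detail.

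**Conclusion.** The point holds as a modest loss of precision in a valid analysis. Section 2.9 fixes an unadjusted t test, while a baseline value already collected, and tied to the outcome by the trial's own reasoning, is left unused. On the pilot SDs, 36 per arm and a difference of 0.09, the gain is about 2 to 4 points of power (78.5% to 80.6% or 82.6%) for an assumed R² of 0.05 to 0.10. There is no gain if R² is zero, and in that case almost no loss. The range rests on an assumption, because the protocol reports no correlation between entry SBP and rCBF.

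A reader might go on to conclude that entry SBP must be added to the minimisation, or that a treatment-by-entry-SBP term is required. Neither follows. A third factor in an 80-patient trial is a debatable trade-off. The varying difference in step 1 of the working does suggest possible effect modification, which a main-effect covariate would not fully capture, but an interaction estimated with about 36 per arm would be imprecise. Both are optional.

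**What to change.** Before database lock, amend section 2.9 so that the key primary analysis is a linear regression of relative rCBF reduction on arm. The covariates are continuous entry SBP (the mean of the two eligibility readings) and the two stenosis factors, level and location, coded as in the minimisation. The treatment effect is the adjusted mean difference with its 95% confidence interval. The unadjusted t test can be kept as a supportive result.

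This costs a sentence in section 2.9 and a few degrees of freedom. It needs no new measurement and no more patients, leaves the allocation and the pressure targets untouched, and can be made even if enrolment has begun.

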### Blinding

2.6

Only the assessors are blinded to this trial because BP targets cannot be concealed to the patients and doctors. The Case Reports Forms (CRFs) will be completed by 2 special assessors who are not involved in the design and assignment. There is no information about the assignment on the CRF and level of BP. The patients and doctors will be informed not to leak the level of BP to the assessors. All data of each group will be analyzed by an analyst who is not involved in this trial.

### Treatment

2.7

After informed fully, participants or their legal surrogate write informed consent. Participants are allocated into intensive group or conservative group after randomization.

#### Intensive group

2.7.1

All patients receive a standardized, stepped, continuous intravenous infusion of antihypertensive agents and frequent BP monitoring. On the basis of the 2015 guidelines of American Heart Association (AHA),^[29]^ the SBP intensive group is to maintain below 140 mm Hg within 1 hour from randomization. The intravenous antihypertensive agents included nitroglycerin, nicardipine, and urapidil hydrochloride. With the use of oral antihypertensive agents after the safety evaluation by doctor group, the doses of intravenous antihypertensive agents are reduced gradually. SBP is maintained from 120 to 140 mm Hg for following 7 days or until hospital discharge if this occurred in advance. About 120 mm Hg is considered as the safe threshold value, lower than which patients may have a risk of low BP. When SBP is lower than 120 mm Hg, we will reduce the velocity of infusion and adjust it according to repeated measurements of BP until SBP maintaining 120 to 140 mm Hg. All of antihypertensive agents are stopped when SBP is lower than 90 mm Hg, and antihypotensive treatments will initiate if necessary. The oral antihypertensive agents are suggested to use to maintain the BP <140 mm Hg upon discharge.

#### Conservative group

2.7.2

The goal of conservative group is to maintain SBP from 140 to 180 mm Hg within 1 hour after randomization. The intermittent or continuous intravenous antihypertensive agents are used to maintain the SBP from 140 to 180 mm Hg and be examined again every 15 minutes. When SBP is more than 180 mm Hg, we will increase the dose of antihypertensive agents or combine different antihypertensive agents.

